## Methods

### *Measurement of symptoms*

Symptoms will be measured during the week before and the week after every visit with the Dutch version of the COPD Symptom Control Questionnaire (CSCQ). Additionally, the questionnaire will be administered by the patients during the visit. Health related Quality of Life will be measured by generic and disease specific instruments.

### *Generic Health related QOL instruments*

At the first visit, after six months and at the final visit patients will be asked to administer the Short Form 36 (SF36) [Ware 1992].

### *Disease specific instruments*

At every visit patients will be asked to administer the St. George Respiratory Questionnaire (SGRQ) [Jones 1992].

### *Lung Function*

Spirometry will be performed according to international guidelines [Quanjer 1993]. A weekly calibrated rolling-seal spirometer, or pneumotachograph (accuracy 50 ml) will be used throughout the study. First, 3 slow inspiratory vital capacity manoeuvres (IVC, use largest value) will be carried out. Second, maximally 5 forced expiratory vital capacity (FVC) manoeuvres will be performed to obtain at least 3 technically satisfactory expiratory flow-volume curves from which FVC does not deviate > 5% from the largest FVC. From these curves, we will use largest values of FVC, forced expiratory volume in 1 second (FEV1), and instantaneous expiratory flows (MEF). Reference values will be obtained from Quanjer *et al.* [1993].

Reversibility of airways obstruction will be measured 20 min after administering 4 single puffs of 100 µg salbutamol per metered dose-inhaler connected to a spacer (Volumatic®), following the same procedures. The response will be expressed as change in FEV1 as percentage of predicted value [Brand 1992].

At 0, 6 and 30 months total lung capacity (TLC), residual volume (RV), functional residual

capacity (FRC), airway resistance (Raw) and specific airway conductance (sGaw) will be measured using a constant volume bodyplethysmograph, according to a standardised method [Quanjer 1993]. Furthermore, the diffusion capacity (transfer factor) for carbon-monoxide ( $TL_{CO}$  and  $K_{CO}$ ) will be measured using the single breathholding method [Quanjer 1993]. The single breath nitrogen wash-out test (slope of phase 3) will be added in Leiden only, as a simple parameter of small airway function with predictive properties for the development and course of COPD [Stanescu 1998].

#### *Exercise capacity*

At 0, 6 and 30 months the 6 minutes walking distance will be determined, in a flat indoor corridor, after 3 practicing attempts [Paggiaro 1998].

#### *Airway hyperresponsiveness*

Airway hyperresponsiveness will be determined using standardized methods [Sterk 1992, Demedts 1998]. This includes challenge tests with methacholine by so-called tidal breathing method. Serial doubling concentrations of methacholine-bromide (0.035-312 mg/ml) will be nebulized by a DeVilbiss 646 jet-nebulizer (filled with 3 ml, connected to an in- and expiratory valve box with an expiratory aerosol filter, operated with pressurized air) with monthly calibrated output of 130 mg/min. The aerosols will be inhaled by tidal breathing during 2 min at 5-min intervals through the mouth with the nose clipped. The response will be measured by  $FEV_1$ . After recording 3 reproducible (within 5% of largest) values of  $FEV_1$  (to obtain mean baseline  $FEV_1$ ), the solvent will be used as first challenge.  $FEV_1$  will be recorded at 30 and 90 s following each challenge, from which the lowest, technically satisfactory value will be used for further analysis. The first concentration of methacholine will be determined from recent guidelines [Demedts 1998]. The challenge will be discontinued if  $FEV_1$  drops by > 20% from mean baseline value. Then the patient will receive 200 µg inhaled salbutamol per MDI, in order to reverse bronchoconstriction. The response of the challenges will be expressed as provocative concentration causing a 20% fall in  $FEV_1$  ( $PC_{20}$ ) by log-linear interpolation. Measurement of the fall in forced vital capacity (delta FVC) at the  $PC_{20}$  level is optional [Gibbons 1996].

#### *Exhaled nitric oxide (NO)*

Exhaled NO levels will be determined at 0, 6 and 30 months using the latest guidelines [Kharitonov 1997, ATS 1999] by a chemiluminescence analyzer (Sievers NOA 270B or Ecophysics CLD 700 AL) [Olin 1999]. The patients will be connected to a closed system with NO-free inspired air (pressurized air < 2 parts per billion: ppb, using a bag-system connected to a 3-way valve), to avoid contamination of the measurements with ambient NO. The patients will perform a slow vital expiratory capacity manoeuvre with a constant expiratory flow of 100 ml/sec against an expiratory resistance of 5 cm H2O. Expiratory NO concentration is sampled continuously from the centre of the mouthpiece at a sample flow of 440 ml/min, and the average concentration will be determined during a period of 10 seconds. At each visit 3 successive recordings will be made at 30-s intervals, from which the mean values of exhaled NO will be used in the analysis.

#### *Induced sputum*

Sputum will be induced and processed according to a validated, and standardized technique [In 't Veen 1996], with some modifications. Prior to sputum induction, baseline FEV1 will be recorded and, for safety reasons, 200 µg salbutamol will be administered through a metered dose inhaler (plus Volumatic®). Hypertonic sodium chloride aerosols (4.5 w/v %) will be generated at room temperature by a DeVilbiss Ultraneb 2000 ultrasonic nebulizer with a calibrated particle size (MMAD 4.5 µm) at maximal output (2.5 ml/min). The aerosols will be administered to the subjects through a 100 cm long tube with an internal diameter of 22 mm, and inhaled via the mouth through a two-way valve (No. 2700; Hans-Rudolph, Kansas City, MO, USA), with the nose clipped. Subsequently, the patients will inhale hypertonic saline aerosols during 3 periods of 5 min. After each inhalation, or as soon as the subjects experience cough, they are asked to blow their nose, to rinse their mouth and throat with water, and to expectorate sputum into a clean plastic container by coughing. Whenever the patients feels discomfort, and after completion of each period FEV1 will be measured, and salbutamol will be administered if FEV1 drops by > 20% from post-salbutamol baseline value.

#### *Sputum processing*

The volume of the induced sputum samples will be determined by weighing. The sample will then be mixed with an equal volume of 0.1% sputolysin (dithiotreitol, DTT, Calbiochem, USA).

To ensure complete homogenization, the samples are placed in a shaking water bath at 37°C for 15 min, once interrupted by gently mixing the sample. The homogenized sputum will be centrifuged (350 x g) for 10 mins at 4°C. The cell-free supernatant will be collected and stored in aliquots at -80°C pending analysis of soluble mediators. The cell pellet will then be resuspended in phosphate-buffered saline (PBS) containing 1 % (w/v) human serum albumin (HSA), pH 7.4, to a final volume of 2-5 ml, followed by filtration through a nylon gauze (pore-size approximately 48 µm, Thompson, Ontario) to remove clumps (filter method to be standardized to a uniform method in Groningen and Leiden). Cell viability and total cell counts are performed by Trypan blue exclusion and using a hemacytometer (use of automated cell count using e.g. Coulter Counter to be discussed). Subsequently the sample will be diluted with PBS (with 2 % w/v HSA, pH 7.4) to a final concentration of 0.3-0.4 x 10^6 cells/ml which is used for preparation of the cytocentrifuge slides (Leiden: 1500 rpm, 3 mins, 50 µl/slide, Shandon 3, Life Sciences International, Veldhoven, The Netherlands; Groningen: 450 rpm, 6 mins, 100 µl/slide; centrifugation speed and equipment to be standardized to a uniform method in Groningen and Leiden). Two slides will be used for Diff-Quik staining to obtain cell differentials, 6-8 slides will be dried and stored at -80°C pending immunohistochemistry analysis.

Differential cell counts of eosinophils, neutrophils, lymphocytes, macro-phages, epithelial and squamous cells are performed on Diff-Quik (choice of staining to be discussed) stained cytopins by a qualified cytopathologist. To correct for the variable salivary contamination, differential leucocyte and cylindric epithelial cell counts will be expressed as a percentage of 500 nucleated cells excluding squamous cells. For each sample, differential cell counts will be performed twice by the same observer, and the mean data will be used in the analysis. A sputum sample will be considered adequate when the percentage squamous cells is less than 80%. To ensure a blind analysis of the sputum samples, all cytocentrifuge slides are coded before analysis by an investigator who is not involved in the counting.

Sputum supernatant will be used to measure soluble mediators (see elsewhere in this section).

### *Bronchoscopy*

Bronchoscopy will be performed using established guidelines in general and those developed for asthma in particular [NHLBI 1985, Harrison 1993, Jarjour 1998]. Smokers are requested

not to smoke their first cigarette on the day of the bronchoscopy before all procedures for investigation are completed. Patients are not allowed to drink or eat food from midnight onwards, except for taking their medication. On arrival for bronchoscopy they will receive 400 µg salbutamol per VolumaticR spacer, 20 mg oral codeine phosphate and 0.5 mg of atropine s.c. [Harrison 1993]. Fifteen minutes later 2 ml of lidocain 1-4% will be instilled in the mouth 3-5 times, on the vocal cords and into the trachea to inhibit coughing. The total lidocain dose must not exceed 3 mg/kg [Ghio 1998]. A flexible bronchoscope will be introduced and bronchoalveolar lavage will be performed into the right middle lobe. 4 Times 50 ml PBS at 30°C will be instilled and after 10 sec of dwelling, it will be removed by gentle suction at 20 cm water pressure or less. Thereafter, 3 times 50 ml of saline will be instilled with dwelling times of 10 sec and each portion of 50 ml of saline will be collected in a tube before the next 50 mls are instilled. All collected BAL will be immediately stored on ice and transported to the laboratory within 15 min after collection. Separate analysis of the first aliquot will be considered.

Bronchial biopsies will be taken from subsegmental carinae in the right or left lower lobe using cup forceps. When possible at least 6 biopsies will be taken (Aleva 1998). Four biopsies will be fixed in 4% neutral buffered formalin, processed and embedded in paraffin. The remaining biopsies will be embedded in Tissue Tek mounting medium, snap frozen in liquid isopentane and finally stored at -80°C.

#### *Processing of BAL fluid*

BAL processing will be performed analogous to the methods used for sputum processing, with the major exception that no DTT/Sputolysin will be used for homogenization.

Immediately upon collection, the BAL fluid will be placed on ice and centrifuged (350 x g) for 10 min at 4°C. The cell-free supernatant will be collected and stored in aliquots at -80°C pending analysis of soluble mediators.

The cell pellet will then be resuspended in phosphate-buffered saline (PBS) containing 1 % (w/v) human serum albumin (HSA), pH 7.4, to a final volume of appr. 1 ml, followed by filtration through a nylon gauze (pore-size approximately 48 µm, Thompson, Ontario) to remove clumps (filter method to be standardized to a uniform method in Groningen and Leiden). Cell viability and total cell counts are performed by Trypan blue exclusion and using a hemacytometer (use of automated cell count using e.g. Coulter Counter to be discussed). Cytospin preparation and

analysis will be performed as described in the Sputum Processing paragraph of this section.

#### *Immunocytochemistry of sputum and BAL cells*

Immunocytochemical staining for cytokines and SLPI as described in the biopsy paragraph will be performed on cytopsin preparations of BAL and sputum. Staining will be performed on formalin-fixed, saponin-permeabilized preparations as described [Grunberg, 1997; details to be discussed between Leiden and Groningen].

#### *Assessment of mediator concentration in sputum and BAL*

For all mediators to be assessed in sputum, initial experiments will be performed to optimize these assays in this complex biological fluid [Grünberg 1997]. These experiments include assessment of the recovery of the mediator and the effect of the reducing agent dithiotreitol on the immunoassay for that specific mediator.

*Cytokine and SLPI levels.* Cytokine levels (IL-1, TNF- $\alpha$ , IL-6, IL-8, IL-4, IFN- $\gamma$ , IL-10 and TGF- $\beta$ ) will be assessed using commercially available immunoassays (Elisa). Levels of SLPI (also known as ALP) will be determined using an Elisa developed in the laboratory of Leiden [Kramps 1984, Wingens 1998]. IL-5 will be quantified with an Elisa procedure developed in Groningen.

*Additional measurements.* Levels of albumin, eosinophil cationic protein (ECP), neutrophil elastase will be determined as described [e.g. Grünberg 1997]. BAL GSH levels will be determined using a spectrophotometric method [Rahman 1998].

#### *Histology*

*Frozen tissue:* Four  $\mu\text{m}$  thick frozen sections will be cut and stored at  $-20^{\circ}\text{C}$  until use. In frozen sections the haematoxylin-eosin (H-E) staining will be used for judging the biopsy quality. These HE slides allow a first impression of the degree of inflammation and give an indication of the types of inflammatory cells. The first screening of biopsies is performed on haematoxylin and eosin stained frozen sections.

*Paraffin-embedded tissue:* From paraffin-embedded tissues 3  $\mu\text{m}$  thick sections are cut. H-E staining will be used for evaluation of overall bronchial architecture, epithelial integrity, and extent of the inflammatory infiltrate. Giemsa stain will be used for further indication of cell populations (eosinophils, mast cells) and PAS diastase stain for basal membranes.

### *Immunohistochemistry*

*Frozen tissue:* Immunohistochemistry is performed on 4 µm frozen sections using two and three step immunoperoxidase protocols. The two-step method is done according to standard operation protocols which are available on request. Briefly, the sections are air-dried overnight and fixed in fresh acetone for 10 mins at room temperature. Sections are washed in phosphate-buffered saline (PBS) after each incubation. Sections are pre-incubated for 30 mins with 10% normal rabbit or goat serum or 1% bovine serum albumin (BSA) to avoid non-specific immunoreactivities. The preincubation fluid is decanted and next, without washing, the primary antibody is incubated for 60 minutes. After washing, the slides are incubated with appropriate secondary antibodies conjugated to horseradish peroxidase. To prevent non-specific staining, 1% normal serum or BSA is added to the second step reagent. The peroxidase label is detected with 3-amino-9-ethylcarbazol or 3,3'-diaminobenzidin together with H2O2. Sections are counter stained with haematoxylin. Negative controls include omission of the primary antibody and application of immunoglobulin-subclass-matched, animal source matched, non-relevant antibodies (if available).

Two different three-step immunoperoxidase protocols are performed to enhance the signal of weakly staining antibodies. The first three-step protocol includes incubation with the second step reagent biotin-labelled secondary antibody followed by incubation with horseradish peroxidase-labelled streptavidin (SBA). The second three-step protocol consists of incubation with horseradish peroxidase-labelled rabbit anti-mouse immunoglobulin antiserum as the second step reagent, followed by horseradish peroxidase-labelled goat or swine anti-rabbit immunoglobulin antiserum as the third step reagent. Other incubation steps are performed as described in the two step immunoperoxidase protocol.

### *Paraffin tissue*

Immunohistochemistry is performed on 3 µm formalin fixed, paraffin embedded lung tissue sections using two or three step immunoperoxidase protocols as described in standard operation protocols. Both protocols are mainly as described for frozen sections. In short, to improve the staining quality of some of the antibodies, antigen retrieval is performed by either proteolytic treatment or by heating in either EDTA (pH 8.0) or citrate buffer (pH 6.0).

Endogenous peroxidase activity is blocked by incubation of the sections for 30 minutes in

H2O2. Subsequent to pretreatment (if necessary), sections are washed and pre-incubated for 30 minutes with 10% normal serum or 1% BSA to avoid non-specific immunoreactivities. Sections are then incubated with the primary antibody overnight. The remainder of the protocols is as described for frozen sections.

### *Biopsy parameters to be studied*

In the following, an overview is given of the possible assessments in biopsies. The number of immunostainings (different antigens) to be performed is determined by the number of available biopsies and their quality.

#### Lymphocytes:

- T cell subsets (CD3, CD4, CD8) and NK cells (CD56)
- Determination of activation of T-cells (CD4, CD8) by staining for T-cell markers and IL2R/CD25

#### Mast cells:

- number and localization of mast cells (Giemsa; tryptase)

#### Neutrophils

- localization and number of neutrophils (neutrophil elastase)

#### Eosinophils:

- number and localization of eosinophils and activated (EG2+) eosinophils

#### Macrophages:

- CD68

#### Epithelium:

- qualitative evaluation (a.o. "intactness")
- morphological changes, incl. metaplasia
- adhesion molecules: ICAM-1, VCAM-1, E-cadherin, EpCam

### Vessels:

-determination of ICAM-1, VCAM-1, E-selectin and P-selectin on vascular endothelium, as these molecules are highly sensitive for regulatory mechanisms in inflammation (in double-staining with CD31).

### Cytokines

IL1, TNF-alpha, IL6, IL8, IL4, IL5, IFN-gamma, IL10, TGF-beta

### Other:

SLPI

### *Quantitative assessments in bronchial biopsies*

All biopsy specimens will be coded and sections will be examined by a single investigator in a blinded fashion, by means of a semi-automated image analysis system using a 200x magnification. Images of areas with well preserved tissue structure and without bronchus associated lymphoid tissue will serve as basis for further computer-aided analysis. For subepithelial analysis, the widest possible zone of maximal 125  $\mu\text{m}$  deep beneath the epithelial basement membrane will be delineated excluding damaged tissue, mucus-secreting glands, and airway smooth muscle (Sont 1996, 1997; Grashoff, 1997; Ten Hacken 1997, 1998). For epithelial analysis, the epithelium will be regarded using the same criteria (Grashoff, 1997). The number of positively staining nucleated inflammatory cells will be counted by a validated full automated procedure (Sont 1998) within the largest possible area per biopsy section (minimally 20,000  $\mu\text{m}^2$ ), and expressed as the number of cells / 0.1  $\text{mm}^2$  (subepithelial) or per 0.1  $\text{mm}^2$  and per mm basement membrane (epithelial). Expression of cytokines and SLPI in the airway epithelium and lamina propria will be semi-quantitatively scored (Sont 1997; de Boer 1998) and quantitatively assessed by densitometric analysis using a digital image analysis system.

### *Computed tomography*

At the start of the study the degree of pulmonary emphysema will be quantified in each COPD patient by CT-scan [Gevenois 1996]. Single slices will be obtained from lung apex to basis (120 kVp, 200 mA, scan time 1 s per slice, 1 mm thickness, 1 cm interval). The acquired

images will be analysed to calculate mean lung density expressed in Hounsfield Units (HU) [Cheung 1997].

## Data analyses

### *Determination of the sample size*

The determination of the sample size is based on detectable differences in the primary outcome variables, the mean inflammatory cell counts in bronchial biopsies between the different treatment groups. Under the assumption that the distributions of (logtransformed) cell counts is approximately normal and the standard deviation in the different treatment groups is approximately equal, the sample size follows:

A sample size of 8-25 patients is needed to detect at least one doubling difference in mean cell number per  $0.1\text{mm}^2$  for a particular inflammatory cell to detect changes within a group ( $\alpha=0.05$ ,  $\text{power}=0.80$ ). A sample size of 13-48 subjects per group is required to detect at least 1 doubling difference in cell number between parallel groups [Sont 1997].

Based on an estimated standard deviation of repeated cell counts in bronchial biopsies of 2.34 fold change, a sample size of 50 per study arm allows us to detect at least a 1.62 fold different increase in number of inflammatory cells/ $0.1\text{ mm}^2$  between two groups.

### *Statistical methods*

*Quality of data:* The quality of the data entry will be checked in a random sample of 10% of the cases.

*Safety:* During the data entry process, all Case Report Forms will be reviewed for possible adverse events (AE). Adverse events are defined as: any unfavourable, unintended event (signs, symptoms, changes in laboratory data) temporarily associated with the administration of the study drug whether or not considered drug related. Examples are signs, symptoms or disorders reflecting adverse event found anywhere in the Case Report Form as notes or comments. All data regarding serious adverse events will be entered into a safety database and analysed at the department of Epidemiology & Statistics of the University of Groningen, 12 months after the start of the study and again after 24 months. The safety variables that will be analysed at those time points are: spontaneously reported adverse events, extended adverse events, question on diagnosis of conditions associated with glucocorticosteroid treatment (hypertension, bone fractures, subcapsular posterior cataract, myopathy and diabetes, and skin bruises on both forearms).

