### *Patient recruitment Leiden*

In Leiden patients with COPD (n=135) will be recruited by advertisement through the media (appendix). Volunteers responding to this advertisement will first be screened by a telephone questionnaire taken by the investigators. When patients meet most of the inclusion criteria and if (in principle) they are willing to participate, they will be asked to visit the hospital to perform spirometry. Subsequently, when FEV1 fulfills the inclusion criteria, the study investigator will provide information to the patient about the study, show a video demonstrating a bronchoscopy procedure and give the patient information form (appendix). One week later the investigator will telephone the patient and ask if he or she is willing to participate. If so, the study investigator will make an appointment for the first visit.

On this first visit the patient and investigator or his/her designee have to sign and date the general informed consent for participation in the study and an informed consent

concerning the three bronchoscopies (appendix).

After the first bronchoscopy the patient will be asked to complete a questionnaire about his or her experiences with this procedure. After having completed this questionnaire the patient will be asked specifically if he or she is still willing to participate in the study (appendix). If this is the case and the patient fulfills all the inclusion criteria and none of the exclusion criteria, the patient will be randomised and the next visit will be planned.

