### *Exclusion criteria*

1. Prior or concomitant history of asthma
2. Alpha-1 antitrypsin deficiency (SZ, ZZ, zero phenotype)
3. Other active lung disease except for mild bronchiectasis; bronchiectasis should not be the main reason for chronic cough and/or sputum production with additional mild obstruction.
4. Contra-indications for elective bronchoscopy, such as O2 saturation <90%, abnormal coagulability, anti-coagulant therapy which cannot be temporarily withheld for performance of bronchoscopy, history of pneumothorax, uncontrolled angina pectoris.
5. Other diseases likely to interfere with the purpose of the study.
6. Inability to keep diary and to understand written and oral instructions in Dutch.

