## Study design

In this prospective, longitudinal, double blind study COPD patients will be followed up for 2.5 years (see *figure*). The study begins as a 3 groups parallel design during 6 months, followed by a 4 groups parallel design during 24 months. The aim is to finish the study with 50 patients in each of the 4 parallel groups at 30 months.

Patients will be treated by the investigator-physician with inhaled corticosteroids (500 µg b.i.d. fluticasone by DiscusR), or inhaled corticosteroids with long-acting  $\beta_2$ -agonist (+ 50 µg b.i.d. salmeterol), or a matching placebo for the first 6 months. Thereafter, half of the corticosteroid group will continue and the other half will receive placebo for 2 years. The patients who will be treated with placebo or inhaled corticosteroids + salmeterol continue their treatment during the complete period of 2.5 years. Rescue treatment will be on demand usage of inhaled inpratropium bromide, which is a standard bronchodilator in COPD [Siafakas 1995].

Subjects who fulfil all inclusion criteria and none of the exclusion criteria (see patient selection) will be allocated to receive placebo, inhaled corticosteroids (equivalents of 500 µg b.i.d. = 1000 µg fluticasone) or inhaled corticosteroids + salmeterol at the beginning of the study using the minimization method. The use of minimization will provide treatment groups that are closely balanced for a number of variables (centre, gender, current smoker, FEV1/IVC < 60%, PC20 methacholine < 2 mg/ml), which might influence the primary and secondary outcome variables [Altman 1995]. The first patient is given a treatment at random. For each subsequent patient we will determine which treatment will lead to better balance between the groups with respect to centre, gender, smoking, FEV1/IVC and PC20. The group with inhaled steroid will be randomly allocated to either the steroid group or the placebo group after 6 months of steroid treatment. Minimization will be performed using a computerized method [Pocock 1983].

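### The adverse event definition is tied to study-drug administration, so complications of baseline procedures done between consent and first dose are not counted as adverse events

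*Protocol*

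**What the plan says.** The Safety paragraph under Statistical methods defines an adverse event as "any unfavourable, unintended event (signs, symptoms, changes in laboratory data) temporarily associated with the administration of the study drug", and adds that a causal link to the drug is not needed: the event has to be "associated with the administration of the study drug whether or not considered drug related". (The third adverb is presumably a slip for temporally.) There is no clause for study procedures and none for the time between consent and first dose.

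On capture, the same paragraph says that "all Case Report Forms will be reviewed for possible adverse events (AE") and gives as examples "signs, symptoms or disorders reflecting adverse event found anywhere in the Case Report Form as notes or comments". On storage and analysis it says "All data regarding serious adverse events will be entered into a safety database", with analyses 12 and 24 months after study start.

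The Measurements section puts biopsies, lavage, sputum induction and methacholine challenge at months 0, 6 and 30. Under Patient recruitment Leiden, consent is signed at the first visit and covers three bronchoscopies. The section continues: "After the first bronchoscopy the patient will be asked to complete a questionnaire about his or her experiences with this procedure". The patient is then asked again whether to go on, and randomisation follows only after that. Item 4 of the Exclusion criteria lists contra-indications for bronchoscopy, among them "history of pneumothorax, uncontrolled angina pectoris".

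**The concern.** The clause that waives causality does not waive timing. Before the first dose there is no drug administration for an event to be associated with, so an event in that interval cannot meet the definition, however serious it is.

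This matters more here than in most drug trials. The primary outcome comes from bronchial biopsies, and the planned procedure combines lavage with at least six biopsies where possible. The exclusion list shows that the protocol regards it as carrying risk. The baseline round is the first evidence on how these patients tolerate it and the only evidence wholly free of treatment, yet it is the round that the definition leaves out. At stake is a correct account of procedure-related harm in consented participants, including those who undergo bronchoscopy and then withdraw before randomisation.

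**Working it through.** The protocol states no figure to reproduce. The check compares the definition with the order of events and then counts procedures.

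**Order of events**

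- *Methacholine challenge.* Study design says that allocation depends on "which treatment will lead to better balance between the groups with respect to centre, gender, smoking". The list goes on to FEV1/IVC and PC20, with a PC20 cut-off of 2 mg/ml. PC20 must therefore be known before a patient is allocated, so the baseline challenge precedes study drug at both centres.
- *First bronchoscopy, Leiden (n=135).* It is stated to come before randomisation, and so before drug.
- *First bronchoscopy, Groningen (n=135).* The order is not stated. The month-0 timing in Measurements makes a pre-drug procedure likely, but this is an inference.
- *Sputum induction.* It is at month 0, and its order relative to the first dose is not stated. Pre-drug is probable.
- *Months 6 and 30.* Drug has started, so the definition can cover complications of these rounds.

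**Route into the safety analysis**

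1. The Case Report Form review looks for adverse events, and the definition decides what is one.
2. The safety database is stated to hold serious adverse events. An event that is not an adverse event is not a serious one.
3. A serious pre-dose complication therefore has no defined route into the database or the 12- and 24-month analyses.
4. A patient who declines after the first bronchoscopy receives no study drug, so no event in that patient ever meets the definition.

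**Share of bronchoscopies**

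Inputs: 270 included and 200 planned at the end (Number of patients); three bronchoscopies per patient (Patient recruitment Leiden). Assumptions: all 270 have the baseline procedure, 200 have the month-30 procedure, and between 200 and 270 have the month-6 procedure.

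- Lower total: 270 + 200 + 200 = 670. Upper total: 270 + 270 + 200 = 740.
- Baseline share: 270/740 = 36% to 270/670 = 40%.
- After drug has started: 200 + 200 = 400 to 270 + 200 = 470.
- Leiden alone, where the order is stated: 135/740 = 18% to 135/670 = 20%.

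Patients who decline after the first bronchoscopy, if not among the 270, would add to the baseline count; the protocol gives no number for them.

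**Number of events**

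This cannot be derived, because the protocol gives no complication rate. For scale only, an assumed 0.5% to 2% would mean 0.005 × 270 = 1.4 to 0.02 × 270 = 5.4 baseline events. The conclusion does not rest on that range.

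**The case against.** The strongest reply is that little would go unseen in practice. All Case Report Forms are reviewed, with no restriction to on-drug visits, and notes anywhere in them count. FEV1 is monitored during the methacholine challenge and sputum induction. The Leiden questionnaire asks about heavy coughing and marked breathlessness during bronchoscopy and invites open remarks, and patients receive it before deciding whether to continue. Investigators would know of a complication at once, may withdraw a patient at their discretion, and would not wait for a 12-month analysis to act. Two of the three bronchoscopy rounds are within reach of the definition.

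Most of this stands. A reader might infer that baseline complications are lost to safety monitoring, or that the questionnaire ignores complications. The documents support neither: events may well be written down, and the questionnaire does collect respiratory symptoms. The reply does not supply a rule that counts and reports these events. A review for adverse events is bounded by their definition, FEV1 monitoring guides the conduct of the test, and the questionnaire is a patient-experience form described only for Leiden.

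A reader might also infer that steroid-associated conditions arising before treatment would later be attributed to it. The protocol lists a separate question on diagnosis of those conditions and does not say when it is asked, so that inference has no basis in the text.

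**Conclusion.** The point holds as a gap in definition and reporting. As worded, complications between consent and first dose are not adverse events and, if serious, have no defined route into the safety database or its analyses. This is firm for the methacholine challenge at both centres and for the Leiden bronchoscopy. It is inferred for the Groningen bronchoscopy and probable for sputum induction.

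If all 270 included patients have the baseline bronchoscopy before drug, it concerns 36% to 40% of planned bronchoscopies. On the order actually stated, for Leiden only, it concerns 18% to 20%.

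One might infer that the safety comparison between arms is distorted. It is not: these events precede treatment, and neither that comparison nor the biopsy outcome is biased. What suffers is the account of procedure risk. The change is worth making because it is cheap and because the trial's primary outcome depends on a repeated invasive procedure.

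**What to change.** Amend the Safety paragraph under Statistical methods as follows.

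- Define an adverse event as any unfavourable, unintended event from signing of consent to the end of follow-up, whether associated with study drug or with a study procedure.
- Add a Case Report Form field for relation to procedure (bronchoscopy, methacholine challenge, sputum induction, other) beside relation to study drug.
- State that events are also recorded for patients who have the first bronchoscopy but are not randomised.
- Report pre-dose and procedure-related events separately from treatment-emergent events, so that the comparison between arms stays as it is.

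The cost is a reworded definition, one form field and a few more events to enter, including some in patients who are never randomised. Sample size, visit schedule and efficacy analysis do not change.
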